## Methods

### Design and study populations

A comparative, parallel-group, randomized, double-blind trial is to be conducted involving an anti-depressant intervention. The experimental group (EG) will use the experimental substance [ketamine IM 0.75 mg/kg, oral placebo (morning), and oral placebo (evening)], while the control group (CG) will use an active treatment administered orally [escitalopram 15 mg (morning), aripiprazole 5 mg (evening) and placebo IM]. The study will be carried out by the Institute of Psychiatry of the University of São Paulo Medical School (HCFMUSP), in conjunction with the Center for Mind Health Studies (NUPE) in the Vale do Itajaí, Santa Catarina state, Brazil. The study is called the KETAMIM project and is Registered Under No. NCT04234776 on the www.ClinicalTrials.gov platform. The study phases and methodological aspects comply with the recommendations of the CONSORT (Consolidated Standard of Reporting Trials) statement and with Good Clinical Practice guidelines (GCP) (65, 66). The study is in running.

The study shall entail 5 phases: (1) Dissemination (P0): patients referred by health professionals, dissemination in the press or online media; (2) Pre-treatment (PI): ~2 weeks for the baseline assessment of candidates for study entry; (3) Therapeutic trial (PII): 4 weeks for ketamine use 3 times weekly and of daily oral medications, as well as placebos for both groups, characterizing acute treatment of the disease; (4) Maintenance (PIII): 24 weeks for weekly ketamine use and maintenance of standard treatment and respective placebos; (5) Post-treatment (PIV): 4 weeks for assessing patients after use of ketamine, maintenance oral medication or placebo.

A total of 88 patients with TRD (≥2 failed trials using anti-depressants, plus ECT as an alternative or otherwise) of moderate-severe intensity [according to criteria of Diagnostic and Statistical Manual of Mental Disorders (DSM-5)], and the diagnosis confirmed by the Portuguese version of the clinical interview of the DSM-IV, will be recruited (67). Patients will be block randomized using a computer-generated list into one of the two interventions (1:1 ratio), EG or CG (68). A nurse blinded to the allocation will administer ketamine or saline IM, placebo orally, or the active treatment, respectively.

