### Measures and outcome variables

The study will assess (given in Table 1):

Sociodemographic variables: gender, marital status, ethnicity, number of children, income, education, and employment.Clinical characteristics over the life course: clinical and psychiatric comorbidities, smoking, family history of mood disorders, prior pharmacological treatment and ECT, number of mood episodes, previous psychiatric admissions, suicide attempts, currently receiving psychotherapy, and history of sexual, or physical abuse.Clinical history: visits to the emergency room, attempted suicides, or psychiatric hospitalizations.The Montgomery-Åsberg Depression Rating Scale (MADRS) (70, 71): will be applied as a primary outcome measure 3× per week for the first month (PII), 1× per week for 6 months (PIII), and 1× per week (PIV) for 1 month.The Hamilton Rating Scale for Depression (HAM-D) (72, 73): will be applied once in PI to assess symptom severity and again 3× per week for 1 month (PII), 1× per week for 6 months (PIII), and 1× per week (PIV) for 1 month.Vital signs (VS): pulse oximetry, heart monitoring, breathing rate, heart rate, and blood pressure will be checked continuously using non-invasive methods. VS to be monitored 3× per week for the 1st month (PII) and 1× week (PIII) for 2 h continuously after completion of each application.Global Clinical Impression (GCI) scale: this will be applied 3× a week for 1 month (PII), 1× week for 6 months (PIII), and 1× week (PIV) to assess disease severity, global improvement of the condition and hence, treatment efficacy (74).Depression Thoughts Scale (DTS): the DTS will be applied at visit one (V-1), V11, and V-39 to assess for thought distortions (75, 76).Clinician-Administered Dissociative States Scale (CADSS): this will provide a measure of the dissociative effects of ketamine and will be applied 3× per week for the 1st month (PII), and 1× per week for 6 months (PIII), ~1 h after application of injections (77).Young's Mania Rating Scale (YMRS): this scale will be employed in this study to assess manic switching as an adverse effect of the medications and applied 3× week for the 1st month (PII) and 1× week for 6 months (PIII), ~1 h after application of injections (78).Brief Psychiatric Rating Scale (BPRS): Sub-item 12 of the scale will be used for detecting the presence of psychotic symptoms arising after application of ketamine, applied 3× week for 1 month (PII) and 1× week (PIII), ~1 h after application of injections (79).Udvalg Kliniske Undersoegelser Side Effect Rating Scale (UKU-SERS): this will be used to determine the presence of side effects of the medications used and will be applied 3× week for the 1st month (PII) and 1× week (PIII) thereafter, around 1 h after application of injections (79).World Health Organization Quality of Life, brief version (WHOQOL-Bref): this scale will be applied at V-1, V-11, and V-35 (80).Sheehan Disability Scale (SDS): this scale will be applied at V-1, V-11, and V-35 (81).

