
**Table 1 T1:** Outcome measurements over time.

**Scales**	**Baseline**	**P1**	**End of P1**	**P2**	**End of P2**	**P3**	**P4**
SCID	x						
MADRS		x		x		x	x
HAM-D	x	x		x		x	x
CGI-S	x	x		x		x	x
DTS	x		x		x		
Physical and neurological exams	x						
Clinical tests and ECG	x						
VS		x		x		x	
UKU-SERS		x		x		x	
BPRS-12		x		x		x	
CADSS		x		x		x	
YOUNG		x		x		x	
WHOQOL-Bref							
SDS	x		x		x		x
Neuropsychological assessment	x				x		

SCID, Structured Clinical Interview for DSM Disorders; MADRS, Montgomery–Åsberg Depression Rating Scale; HAM-D, Hamilton Depression Scale; CGI-S, Clinical Global Impression—Severity; DTS, Depressed Thoughts Scale; VS, Vital Signs; UKU-SERS, Udvalg for Kliniske Undersøgelser Side Effect Rating Scale; BPRS-12, Brief Psychiatric Rating Scale; CADSS, Clinician-Administered Dissociative States Scale; YOUNG, Young Mania Rating Scale; WHOQOL, World Health Organization Quality-of-Life scale; SDS, Sheehan Disability Scale.

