### Intervention

Two groups will be formed: a study group and an active control group. The study group will receive dextroketamine chloralhydrate IM (0.75 mg/kg) plus 2 placebo tablets orally, one in the morning and the other at night. The active control group will receive saline solution IM plus one of the alternative therapies for TRD: escitalopram 15 mg (morning) or aripiprazole 5 mg (night) (10). Injections will be applied alternately to gluteal muscles in the external upper quadrants. For 4 weeks (1 month), applications will be applied on Mondays, Wednesdays, and Fridays (giving a total of 12 interventions). For the ensuing 6 months, applications will be weekly (giving a total of 24 interventions). For 4 weeks (1 month), participants will continue to receive the tablets (active treatment or placebo) and be monitored. Safety parameters: vital signs will be monitored continuously by the researchers for 2 h post-application: fingertip pulse oximetry, heart rate, breathing rate, blood pressure, and electrocardiography. Abnormal blood pressure will be defined as low <90/60 mmHg and high >140/90 mmHg. Abnormal heart rate will be defined as <60 or >100 bpm. Abnormal breathing rate will be defined as <10 cycles/min or >20 cycles/min. Low oxygen saturation will be defined as levels <95%. Collateral symptoms such as nausea and vomiting will be managed using ondansetron 8 mg sublingually (SL). Individuals presenting episodes of anxiety, hallucinations, or intense dissociative effects will be given clonazepam SL 0.25 mg. An emergency team will be deployed in the event of serious acute events such as heart arrhythmia or prolonged hypertension. Patients will be placed under observation in a quiet comfortable environment and will be cleared to leave after 2 h, accompanied by a competent adult.

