### Reasons for withdrawal or termination

Subjects who meet one or more of the criteria outlined below will be withdrawn from the study:

Intolerance to medications;Abnormal results on lab tests;Serious adverse event;The above-mentioned items will be assessed individually by the team according to medical criteria. Prolonged arterial hypertension, serious allergies, abnormal heart rate, or worsening of pre-existing diseases, among others, will be checked. Manic switching, imminent risk of suicide, attempted suicide, severe psychotic symptoms, aggressiveness, etc. will constitute grounds for study withdrawal.Relapse or lack of response in Phases II or III. Lack of response will be defined as reduction or maintenance of scores on the index scale of ≤25%, whereas relapse will be the attainment of scores <50% in individuals who had achieved remission or response during the study.Two consecutive visits missed;Withdrawal of consent for the study.

Patients who discontinue the study shall be given guidance to continue outpatient psychiatric treatment.

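### The side-effect and mania scales stop at the last injection, so the 4-week post-treatment phase (PIV) has no scale-based harm rating, and Table 1 does not fit the text under either reading of its phase labels

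*Protocol article*

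**What the plan says.** The Measures and outcome variables section gives each scale its own schedule by phase. MADRS, HAM-D and the global impression scale run through PII, PIII and, weekly, PIV. UKU-SERS does not: it "will be applied 3× week for the 1st month (PII) and 1× week (PIII) thereafter, around 1 h after application of injections". YMRS is likewise limited to PII and PIII, about an hour after injections.

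The stated purposes are broader than ketamine. Of UKU-SERS the article says "this will be used to determine the presence of side effects of the medications used". YMRS is included "to assess manic switching as an adverse effect of the medications".

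On what patients receive in the last month, the Intervention section says: "For 4 weeks (1 month), participants will continue to receive the tablets (active treatment or placebo) and be monitored". Design and study populations labels the same month post-treatment and describes it as "4 weeks for assessing patients after use of ketamine, maintenance oral medication or placebo".

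Table 1 ("Outcome measurements over time") has the columns Baseline, P1, End of P1, P2, End of P2, P3 and P4, whereas the text defines phases P0 and PI to PIV. UKU-SERS and the Young scale are marked in P1, P2 and P3 and are blank in P4.

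**The concern.** The two scales meant to record side effects and manic switching end about an hour after the final injection. By the Intervention section, control patients then take active tablets for another month, and patients in the ketamine arm enter their only observation after 36 injections. Both arms are still seen weekly for depression ratings, so the visits exist but the harm scales are not used at them. The main analysis is described as running from the first to the final visit. PIV therefore appears to contribute to efficacy without a matching structured rating of harm.

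Site staff who turn to Table 1 would not get a clear answer. Depending on how its labels are read, they would either rate both scales in PIV or not, and would do cognitive testing after 4 or after 28 weeks of treatment.

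**Working it through.** **Inputs.** From Intervention: injections three times weekly for 4 weeks, then weekly for 24 weeks, then 4 weeks with tablets only. From Measures and outcome variables: UKU-SERS and YMRS at injection visits in PII and PIII; MADRS, HAM-D and the global impression scale also weekly in PIV.

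**Ratings per patient under the text.**
- PII: 3 × 4 = 12. PIII: 1 × 24 = 24. These reproduce the article's own counts of 12 and 24 injections.
- UKU-SERS and YMRS: 12 + 24 = 36 of each, plus 0 in PIV.
- MADRS in PIV: 1 × 4 = 4.
- With weekly rating in PIV, UKU-SERS and YMRS would become 36 + 4 = 40 of each.

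**Oral exposure without these scales.** Tablet weeks: 4 + 24 + 4 = 32. Weeks without UKU-SERS or YMRS: 4. Share: 4/32 = 12.5%. This holds only if tablets continue in PIV.

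**Visit numbers.** The Statistical analysis section numbers visits from 0. Then PII is V0–V11, PIII is V12–V35 and PIV is V36–V39. These limits coincide with V-11, V-35 and V-39 named in the text, so the text's own schedule is coherent.

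**Table 1, literal reading (P1–P4 = PI–PIV).**
- UKU-SERS and YMRS are blank in PIV: agrees with the text.
- Both scales, together with the dissociation scale and vital signs, are marked in PI, before any injection: conflicts with the text.
- Neuropsychological testing at End of P2 falls after the 4-week acute phase. The Cognitive assessments section places it at the end of PIII, after 4 + 24 = 28 weeks: conflict.

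**Table 1, shifted reading (P1–P3 = PII–PIV).**
- Neuropsychological testing at End of P2 now falls at the end of PIII: agrees.
- The disability scale at End of P1 and End of P2 now matches V-11 and V-35: agrees.
- UKU-SERS and YMRS are marked in PIV: conflicts with the text.
- The dissociation scale and vital signs are marked in a month without injections: conflicts with the text.
- P4 corresponds to no phase.

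**Under both readings.** The disability scale is marked in P4, although the text's last rating is V-35. The depressive thoughts scale has its last mark at End of P2, although the text's last rating is V-39. Neither reading brings the table into line with the text.

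**The case against.** The strongest reply has three parts.

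First, the safety objective in Study hypotheses concerns ketamine during acute and maintenance treatment. PIV lies outside it, and ratings through PII and PIII match it. This stands: the article does not break a stated objective. But the scales' own descriptions cover the medications generally, and the tablets outlast the injections.

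Second, harm in PIV is not ignored. Patients are to be monitored; intolerance, serious adverse events, manic switching, attempted suicide and severe psychotic symptoms are withdrawal grounds, with no limit to PII or PIII stated for them; and three clinical scales continue weekly. General adverse-event reporting may also sit in the full protocol, which is not shown. This stands too. A reader might infer that late harm goes unrecorded or cannot be reported; the documents do not support that. What is missing is a scheduled structured rating.

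Third, Table 1 read literally agrees with the text on PIV. That is correct, so a reader who infers that the table plainly contradicts the text on this point goes too far. The contradiction on PIV arises only under the shifted labels, although the neuropsychology and disability rows favour that reading.

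Two further inferences are not supported. The BPRS item is described as detecting psychotic symptoms after ketamine is given, so limiting it to injection visits follows from its purpose. The relapse criterion, limited to Phases II and III, is a withdrawal rule and a matter of clinical management; worsening in PIV is still measured by weekly MADRS.

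**Conclusion.** The point holds in a limited form. By the text, UKU-SERS and YMRS are each rated 36 times and never in PIV, while MADRS is rated there 4 times. The gap is 4 weeks: 12.5% of control-arm oral exposure and all of the follow-up after ketamine. The last rating of each scale comes about an hour after the final injection, so effects that emerge later have no scheduled scale to record them. Table 1 cannot be matched to the text under either reading.

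The 12.5% assumes that tablets continue in PIV, as the Intervention section says. The other description of PIV can be read as after all treatment, or as after ketamine with oral treatment maintained; if tablets stop, the percentage no longer applies, but the gap in post-ketamine follow-up remains. The visit numbers assume counting from 0. The primary outcome is not affected.

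**What to change.** 1. Add UKU-SERS and YMRS to the weekly PIV visits already held, in both arms, with each rating covering the time since the last visit. The first would then cover the interval after the final injection.
2. Relabel the columns of Table 1 with the phases PI–PIV as defined in Design and study populations, and correct its rows so that they agree with Measures and outcome variables and with Cognitive assessments.
3. Reconcile Design and study populations with Intervention on whether tablets continue in PIV. Which is intended is for the sponsor to state.

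The cost is about 4 more ratings of each scale per patient, at most 88 × 4 = 352 of each if all 88 patients reach PIV, with no new visits, plus an amendment to the wording and the table.

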### Randomization and allocation

Randomization will be based on a computer-generated scheme, balanced by the use of randomly permutated blocks and stratified by the statistician of the Institute of Psychiatry of the FMUSP to receive ketamine IM or active treatment at a 1:1 ratio (82).

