### Sample size calculation

The sample size was calculated based on a similarly designed RCT (45). Assuming a statistical power of 90% with a clinically significant minimum effect of 0.5 (Cohen's d) and alpha 5%, a total of 88 subjects will be needed (44 in the EG and 44 in the CG). Given this is a long-duration study, a drop-out rate of 10–20% was estimated.

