### Statistical analysis

All analyzes will be performed using the Statistical Package for the Social Sciences-SPSS® (82). Specific and sociodemographic variables will be expressed generally and between intervention groups in relative and absolute frequencies, means, medians, standard deviation, and 95% confidence interval. Continuous variables will be evaluated by the *T*-student or U-Mann Whitney-test according to their distribution and the qualitative ones by the *X*^2^-test. The distribution of variables will be evaluated using the Shapiro Wilk. The global significance level adopted is 0.05. To determine the effects of intervention throughout the study (main outcome and other scales), repeated measures ANOVA (two-way) will be applied, considering the temporal effect of visits (v-0 to v-final) and the intervention effect (EG × CG). In identifying the significant interaction effect, one-way repeated measures ANOVA test or its non-parametric alternative (Friedmann test) will be performed to verify that the effect is independent of treatment. Contingency tables and *X*^2^-tests will be applied to compare responders and non-responders in the intervention groups. Analysis using intent-to-treat (ITT) will be employed to assess the results (83). Vital signs will be assessed using two repeated measures ANOVA (two-way). First, considering the effect of the intervention immediately (3 evaluations at each visit) and the second, evaluating the effect of the intervention on VS over time (acute and maintenance treatment).

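### Randomisation is described as stratified, but the MADRS model contains only visit and arm; if the strata are prognostic, the between-patient arm test is conservative and some power is lost

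*Protocol article*

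**What the plan says.** Three places in the Protocol article bear on this.

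- **Randomization and allocation:** the computer-generated scheme is "balanced by the use of randomly permutated blocks and stratified by the statistician of the Institute of Psychiatry". No stratification factor follows.
- **Design and study populations:** "Patients will be block randomized using a computer-generated list into one of the two interventions (1:1 ratio". Strata are not mentioned.
- **Statistical analysis:** for the main outcome and the other scales, "repeated measures ANOVA (two-way) will be applied, considering the temporal effect of visits (v-0 to v-final) and the intervention effect (EG × CG". The next step is conditional on the interaction: "In identifying the significant interaction effect, one-way repeated measures ANOVA test" or a Friedman test follows. No stratum term or other covariate is mentioned. Simple between-group comparisons use t-, Mann-Whitney and chi-square tests. On the level: "The global significance level adopted is 0.05".

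The sample size section gives the planning inputs: "Assuming a statistical power of 90% with a clinically significant minimum effect of 0.5 (Cohen's d) and alpha 5" per cent, from which "a total of 88 subjects will be needed (44 in the EG and 44 in the CG".

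**The concern.** Balancing the arms within strata removes the stratum differences from the true sampling variation of the arm difference. A model that omits the strata leaves those differences in its error term. The estimated standard error is then larger than the true one, so the test rejects less often than its nominal level and the interval is wider than it need be.

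What is at stake is efficiency. It matters somewhat more here because the principal hypothesis is that the two treatments have similar efficacy. A wider interval makes similarity harder to support, and an insensitive test of difference makes a non-significant result easier to misread as similarity.

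The text also needs reconciling whatever the size of the effect. If strata were used, the stated model does not follow the stated design. If they were not, the randomisation section is worded wrongly.

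**Working it through.** **Inputs.** From the document: 44 per arm, d = 0.5, alpha 0.05. Two-sided testing is assumed, because sidedness is not stated. R² is the share of between-patient variance explained by the strata. It is an assumption, taken from 0 to 0.3, because no factor is named and no prognostic strength is given. Exact balance of arms within strata is also assumed.

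**The plan's own figure.** The standard two-sample formula gives n per arm = 2(1.960 + 1.282)²/0.5² = 84.1, rounded up to 85, or 170 in total. This does not reproduce 88. With 44 per arm the non-centrality is 0.5/√(2/44) = 2.345, and power is Φ(2.345 − 1.960) = 65%. This 65% is the starting point for the main table.

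**Between-patient arm effect.** With total variance set to 1, the true variance per patient relevant to the arm difference is 1 − R², while the unadjusted model estimates 1.

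- True type I error, strata omitted: 2[1 − Φ(1.96/√(1 − R²))]
- Power, strata omitted: Φ((2.345 − 1.96)/√(1 − R²))
- Power, strata included: Φ(2.345/√(1 − R²) − 1.96)
- Excess interval width: 1/√(1 − R²) − 1

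| R² | True alpha, omitted | Power, omitted | Power, included | Difference (points) | Excess width |
|---|---|---|---|---|---|
| 0 | 5.0% | 65.0% | 65.0% | 0 | 0% |
| 0.05 | 4.4% | 65.4% | 67.2% | 1.8 | 3% |
| 0.10 | 3.9% | 65.8% | 69.6% | 3.8 | 5% |
| 0.20 | 2.8% | 66.7% | 74.6% | 7.9 | 12% |
| 0.30 | 1.9% | 67.7% | 80.0% | 12.3 | 20% |

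**Check by simulation.** The set-up was 88 patients, 5 visits, within-patient correlation 0.5 and two equal strata balanced by arm, with the arm main effect tested on patient means.

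| R² | Alpha, omitted | Alpha, included | Power, omitted | Power, included |
|---|---|---|---|---|
| 0 | 5.1% | 5.1% | 65.0% | 65.1% |
| 0.10 | 3.8% | 4.7% | 63.9% | 67.9% |
| 0.20 | 2.8% | 5.0% | 65.7% | 74.1% |
| 0.30 | 1.7% | 4.6% | 65.1% | 78.7% |

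These agree with the closed form to within about 3 points.

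**Visit-by-arm interaction.** This is tested on each patient's deviations from his or her own mean. A stratum effect that is constant over time is part of that mean and cancels. In the same simulation, with the strata omitted, the interaction test had alpha between 4.6% and 5.2% and power between 52% and 53% at every R².

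**Sensitivity to the starting power.** The number 88 can be approached in another way. A between-arm repeated-measures formula with 12 + 24 + 4 = 40 assessments, f = 0.25 and correlation 0.5 has non-centrality 0.0625 × 88 × 40/(1 + 39 × 0.5) = 10.73 and power 89.96%. The document states no correlation, so this is only an illustration. Putting √10.73 = 3.276 in place of 2.345 gives, strata omitted against included, 91.7% against 93.2% at R² = 0.10 and 94.2% against 97.5% at R² = 0.30. The loss is then about 1.5 to 3.3 points. True alpha is the same as in the first table.

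**The case against.** The strongest reply has four parts.

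1. **The premise is uncertain.** The randomisation sentence says who stratified, not by what, and may be loose wording for allocation. The design section is compatible with no strata. This stands as a reason to ask, and it is why the size cannot be fixed. It does not remove the need to correct one text or the other.

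2. **The plan acts on the interaction.** With visits running from baseline, an effect on change appears as visit by arm, where a constant stratum effect cancels. This stands. A reader might infer that the whole MADRS analysis is conservative; the document does not support that. It does name the intervention effect as a model effect, so the affected test is in the plan.

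3. **The loss is hypothetical.** At R² = 0 it is nil, at 0.05 it is under 2 points, and incomplete blocks among 88 patients need not give the exact balance that the formula assumes. This stands. A reader might infer a certain loss of power, but nothing in the document shows that the strata are prognostic.

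4. **An article condenses.** Factor names and full covariate lists are commonly left to a full protocol or analysis plan. This stands for the missing factor name taken alone, and a document not shown could add the term. The point here is narrower: a stated model does not match a stated design.

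**Conclusion.** The point holds conditionally. The article says that randomisation is stratified and gives a primary model with visit and intervention only. If the strata are prognostic, the test of the between-patient intervention effect is conservative and its interval too wide. Over an assumed R² of 0 to 0.3, true alpha lies between 5% and 1.9%. The power forgone is 0 to about 12 points on the single-comparison approximation with 44 per arm, and less if the starting power is higher than 65%.

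Two stronger readings should be set aside. A reader might infer a threat to validity, but type I error is not inflated, so the issue is one of efficiency. A reader might also infer that adjustment would rescue the sample size. At R² of 0.3, adjusted power reaches 80%, not the stated 90%; the gap between 88 patients and the stated inputs is a separate matter.

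**What to change.** 1. In Randomization and allocation, state whether strata were used and, if so, name the factor or factors. Make Design and study populations agree.
2. If strata were used, add the factor or factors as between-subject fixed effects to the repeated-measures models for MADRS and the other scales in Statistical analysis. Add their interaction with visit if they may alter the time course.
3. The t-, Mann-Whitney and chi-square tests need not change, since they take no fixed effects. A stratified counterpart, such as Cochran-Mantel-Haenszel for responders, is optional.
4. If no strata were used, delete the reference to stratification. The model can then stand on this point.

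The cost is a sentence or two of text and a few degrees of freedom. If the strata turn out not to be prognostic, almost nothing is lost by including them.
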